**Figure 4 F4:**
[figure not shown]
**O****utline of DESPATCH intervention and its delivery: third phase**.

Each academic detailing session comprised standardised prompts related to the mailed materials addressing barriers to the use of anticoagulation in their practice. During each academic detailing session, GPs were invited to identify a patient with atrial fibrillation about whose management they wish to receive specific feedback. The medical peers used a standardised pro forma for each GP-identified patient, requesting and recording information from GPs about patient medical history, stroke risk factors, current antithrombotic treatments, adverse events on antithrombotics, and any reasons for not prescribing anticoagulants. Academic detailers were instructed to calculate the CHADS2 score and provide evidence-based feedback using standardised information on antithrombotic treatment.

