### Expert decisional support

After each academic detailing session, medical peers returned completed pro formas to the research team. On behalf of the GPs, the research team sought feedback from experts about the management of these patients. Experts comprised medical specialists in neurology and cardiology. Information from each de-identified completed pro forma was summarised onto one page. For each patient, a CHADS2 score and annual ischaemic stroke risk were reported. The one-page summary was emailed to specialists to provide written feedback, and this feedback was then mailed to GPs via the research team (Additional File 1).

During the development of our intervention, another team published a protocol for a cluster randomised controlled trial (cRCT) in primary care, evaluating a faxed one-page evidence-based statement referring to specific patients, with or without the signatures of local 'opinion leaders' [29]. The protocol provided a model for delivering this aspect of the intervention.

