## Ascertainment of atrial fibrillation

Using a standardised audit form, the trained nurse auditors, blinded to the study design, aims, and group allocation, will apply a standardised checklist to first determine whether or not a patient has a recorded diagnosis of atrial fibrillation.

Any diagnosis of atrial fibrillation noted in the medical record, appearing in specified test results (electrocardiograms, Holter monitoring, and transesophageal or transthoracic echocardiograms), referral letters, specialist correspondence, or hospital discharge summaries, will identify patients as having atrial fibrillation. The date of the recorded entry, correspondence, or test result will be noted. In the absence of a diagnosis of atrial fibrillation, atrial flutter will be recorded where noted in the medical record.

For the purposes of distinguishing between cases of atrial fibrillation (or atrial flutter) first noted before or after randomisation, nurses are instructed to exhaust the standardised checklist and proceed through a set of instructions directing them to note if atrial fibrillation was diagnosed on or after a chosen date (October 1, 2009), approximating the date of randomisation on October 13, 2009. Patients whose diagnosis of atrial fibrillation was noted only after randomisation will be considered 'newly diagnosed' and excluded, minimising the possibility of biased patient selection postrandomisation. To maintain blinding of the study design and aims, nurses are informed that one of the project aims is to distinguish between newly diagnosed and established cases of atrial fibrillation (or atrial flutter) to determine the incidence of newly diagnosed cases over a period of 12 months. Nurses are instructed to collect data on all cases of atrial fibrillation (or atrial flutter), irrespective of when the diagnosis was noted.

When collecting information about comorbidities (see below), nurses will also record diagnoses of mitral stenosis, mixed mitral valve disease, rheumatic mitral valve disease, or mitral valve replacement, allowing the researchers to exclude these cases as examples of valvular atrial fibrillation. Cases of atrial flutter, in the absence of a recorded diagnosis of atrial fibrillation, will be regarded as equivalent to a diagnosis of atrial fibrillation in keeping with international evidence-based guidelines recommending identical management of these cardiac arrhythmias [5].

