## Primary outcome

We have defined the primary outcome as the proportion of patients with atrial fibrillation over the age of 65 years noted to be on treatment with oral anticoagulation at two prespecified time periods: (1) at *any *time in the 12 months from the date of randomisation and (2) currently (as defined below). Medical record notations of oral anticoagulant treatment, including prescriptions, consultation notes, referral letters, correspondence from specialists, hospital discharge summaries, and dates of INR results (with INR levels greater than 1.2), will be considered to be an indication that the patient is receiving anticoagulation on the date of the notation.

Anticoagulation indicated in the last three months of the 12-month period from randomisation will be considered 'current' if there is no noted suspension of warfarin or if a suspension is noted to be temporary. Three months is chosen as current to ensure adequate ascertainment of our anticoagulation indicators, such as doctor's follow-up notations, prescriptions, and correspondence.

At the time the study was devised and at the time of writing, warfarin was the only locally approved anticoagulant for the management of atrial fibrillation. During the study period, two fixed-dose oral anticoagulants (dabigatran and rivaroxaban) [33,34] had been under investigation in randomised controlled trials. Therefore, in addition to warfarin, these two treatments will also be considered as oral anticoagulant treatment in the unlikely event that patients in this project are receiving the drugs in trials or are receiving these treatments off-label. Other types of anticoagulation, such as clexane (enoxaparin) and heparin, will not be considered in our primary or secondary outcome assessment. These medications are not administered orally and are not usually indicated for long-term anticoagulation in NVAF.

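### Specialist correspondence counts as evidence of anticoagulation, and no rule excludes the specialist letters that the intervention itself sends to one arm during the outcome window

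*Protocol article*

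**What the plan says.** **Outcome rule (Protocol article, Primary outcome).** The accepted evidence is a notation of oral anticoagulant treatment in one of several sources. The list opens with prescriptions and consultation notes and goes on: "referral letters, correspondence from specialists, hospital discharge summaries, and dates of INR results (with INR levels greater than 1.2), will be considered". Each such notation "will be considered to be an indication that the patient is receiving anticoagulation on the date of the notation". One notation in the 12 months makes the patient a success on the any-time definition. A notation in the last three months makes the patient a current user, unless a suspension that is not temporary is noted.

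**Intervention (Academic detailing; Expert decisional support).** There are three telephone sessions. "During each academic detailing session, GPs were invited to identify a patient with atrial fibrillation about whose management they wish to receive specific feedback". Then: "Information from each de-identified completed pro forma was summarised onto one page". "The one-page summary was emailed to specialists to provide written feedback, and this feedback was then mailed to GPs via the research team".

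**Timing (The DESPATCH intervention; Follow-up).** Delivery took place within 12 months of randomisation, and the outcome window is the 12 months from randomisation.

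**Control arm (Seminars; Ethical considerations).** Control GPs were mailed guidelines and invited to a seminar on another topic. They are promised specialist support as waiting-list controls, but the article does not say when this falls relative to the audit.

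**Audit (Ascertainment of atrial fibrillation).** The outcome is extracted by "the trained nurse auditors, blinded to the study design, aims, and group allocation".

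**The concern.** The intervention produces documents of a type that the outcome rule accepts, in one arm, inside the outcome window. The rule names other exclusions, such as enoxaparin and heparin, but is silent on the trial's own letters. An auditor who does not know the design has no stated ground for discounting a letter from a neurologist or cardiologist that discusses warfarin.

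If a letter is on file, three things could go wrong:

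- A recommendation, or a mention of past use, is read as current use. The error then favours the intervention.
- The letter correctly reports use that the rest of the record documents poorly. That is no false positive, but true use becomes easier to detect in one arm.
- The letter reveals the study's purpose or the practice's allocation.

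The any-time definition is the most exposed, because one notation is enough. Other outcomes share the evidence. The appropriateness outcome uses the same any-time and current periods. The percentage-of-time outcome carries a notation forward for up to three months, so one false notation could credit about 90 of 365 days.

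**Working it through.** **1. The plan's own figures.** For 60% vs 50%, 80% power and 5% two-sided (sidedness is not stated; two-sided is assumed):

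- Without continuity correction: n = (1.960 × √(2 × 0.55 × 0.45) + 0.842 × √(0.25 + 0.24))² / 0.10² = 387.3.
- With continuity correction: (387.3 / 4) × (1 + √(1 + 4 / (387.3 × 0.10)))² = 407.1, which matches the stated 407.
- Design effect: 1 + (25 − 1) × 0.04 = 1.96. Then 407 × 1.96 = 797.7, or 798, and 798 / 0.9 = 886.7, or 887. Both match.

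The sample size is not in question. It supplies the effective n of 407 per arm used in step 4.

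**2. Ceiling on patients with a letter.** Three sessions with one patient each, over an estimated 20 eligible patients per GP (Sample size): 3 / 20 = 15% of intervention patients. This requires every GP to name three different patients, all of them in the audited cohort.

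**3. Spurious difference.** Excess = 15% × share filed × share not on treatment × share misread as use. The documents give none of the last three shares. The ranges are assumptions: filed 25% to 50%, not treated 30% to 50%, misread 10% to 100%.

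| Misread | Low (filed 25%, untreated 30%) | High (filed 50%, untreated 50%) |
|---|---|---|
| 10% | 15 × 0.25 × 0.30 × 0.10 = 0.11 points | 15 × 0.50 × 0.50 × 0.10 = 0.375 points |
| 25% | 15 × 0.25 × 0.30 × 0.25 = 0.28 points | 15 × 0.50 × 0.50 × 0.25 = 0.94 points |
| 100% | 15 × 0.25 × 0.30 × 1 = 1.1 points | 15 × 0.50 × 0.50 × 1 = 3.75 points |

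So the range is about 0.1 to 0.9 points if 10% to 25% of such letters are misread, and 1.1 to 3.75 points if all are.

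**4. Effect on the test.** Take no true effect (50% in both arms), 407 effective patients per arm and the normal approximation. The standard error is √(2 × 0.25 / 407) = 3.5 points, so significance needs a difference of about 1.96 × 3.5 = 6.9 points. The two-sided false-positive rate is then:

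- excess 0.11 points: 5.0%
- excess 0.94 points: 5.8%
- excess 1.1 points: 6.2%
- excess 3.75 points: 18.8%; the upper tail is Φ((3.75 − 6.9) / 3.5), about 0.19, and the lower tail adds about 0.001.

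**The case against.** **The rule asks for treatment, not for a letter.** A reader might infer that any specialist letter counts as proof of anticoagulation, or that the rule cannot tell a recommended drug from a taken one. The wording does not support this. What counts is a notation of treatment, taken as an indication of use, and correspondence is only one place to find it. A letter that merely recommends warfarin does not qualify, so a false positive requires an auditor to misapply the rule. This stands, and it is why the misreading share belongs in the calculation.

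**Filing is not stated.** The specialist worked from a de-identified summary, and nothing says that the reply carried a name or entered the patient's record. This stands too, although the GP chose the patient and could file the reply.

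**The letter may help the auditor.** The pro forma records current treatments and reasons for not prescribing. If these carry over, the letter could show that an untreated patient is untreated.

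**The 15% is a ceiling.** GPs could decline or repeat a patient, or name one outside the cohort: too young, newly diagnosed, valvular or opted out. An untreated patient who truly starts within the 12 months is correctly a success, so the assumed untreated share may also be too high.

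**Blinding.** A reader might infer that a filed letter defeats the blinding. That goes too far. Auditors are given another stated aim, and one letter need not show that there are two arms or which arm this is. It could do so; the article does not show that it would.

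**It may be in the audit manual.** The standardised form and instructions are not shown and may cover this. But the published rule is detailed about what counts and what does not, and as written it leaves the trial's letters inside an accepted category.

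**Conclusion.** The point holds as an open route for one-sided ascertainment in the primary outcome. Specialist correspondence is accepted evidence, the intervention sends specialist letters to one arm within the window, and the article states no rule that excludes them. Misreading and easier detection would both raise the intervention arm's observed rate.

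The documents do not show that the primary result is biased. The size is unknown: at most 15% of intervention patients could have a letter, and the spurious difference is about 0.1 to 3.75 points against the 10-point target. The upper end needs half of the letters filed, half of those patients untreated and every such letter misread. With 10% to 25% misread it stays below 1 point, and the false-positive rate stays below 6%. Easier detection of true use and possible unblinding are not in these figures and cannot be quantified from the article. The point is worth settling before the analysis because the outcome is primary and the remedy is cheap.

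**What to change.** - In the Primary outcome section and on the audit form, state that study-generated documents (expert feedback, pro formas, mailed materials) are never evidence of anticoagulant use, and that a recommendation alone is not use. Word the audit instruction so that it does not disclose the design or the arms.
- Have auditors record the source type of each notation, and whether they saw study material.
- Prespecify a sensitivity analysis of the primary outcome, for both the any-time and the current definition, that accepts only a prescription or an INR result above 1.2.
- Do not ask practices to remove study documents before the audit. Unblinded staff would then be altering records mainly in one arm.

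The sample size is unchanged. The cost is one audit rule, two extra fields and one extra analysis, with slightly lower ascertainment in that analysis. The Discussion says that data collection has commenced, so if the form does not already capture source type, records audited so far may need a second look.

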## Secondary outcomes

### The proportion of patients prescribed antithrombotic treatment judged as 'appropriate' according to stroke risk

Stroke risk will be assessed using a validated, evidence-based risk stratification scheme and evidence-based guidelines. At the time the study was initiated, the evidence-based risk stratification scheme often endorsed by national and international guidelines was the CHADS2 score [35]. Local guidelines recommend anticoagulation with warfarin for patients with a CHADS2 score of 2 or higher, aspirin or warfarin for patients with a CHADS2 score of 1, and aspirin for patients with a CHADS2 score of 0. This outcome will be measured for *any *time within 12 months of postrandomisation and for current use, as defined above. Only comorbidities noted in the medical record prior to the date of randomisation will be considered in the calculation of the CHADS2 score.

### The proportion of patients prescribed antithrombotic treatment judged as appropriate as above, incorporating quality control criteria for anticoagulation use

If patients are receiving anticoagulation with warfarin, antithrombotic treatment will be judged to be appropriate only where patients receive warfarin according to the above criteria for appropriate antithrombotic treatment *and *where quality control of warfarin is adequate. Adapting a definition devised by McAlister *et al*. [24], quality control of warfarin will be considered adequate if INR levels are measured at least monthly, from the first date patients are known to be taking warfarin during the 12-month follow-up period, and if at least 67% of INR levels are between 2.0 and 3.0. A minimum of monthly INR measurements are recommended in local guidelines [32] and 67% of INR readings within the therapeutic range has been achieved in randomised evaluations of warfarin [6,8]. We will not impose any minimum required number of INR results to calculate this outcome. In the instance of patients receiving new fixed-dose anticoagulants, quality control criteria will be assumed to be met without INR evaluation, as these medications do not require monitoring.

### The percentage of time patients used oral anticoagulation over the 12-month postrandomisation follow-up period

The first recorded date of oral anticoagulation noted in the medical record during the 12-month follow-up period will be considered the index date. We will assume anticoagulation use recorded up to three months before randomisation will indicate anticoagulation was used on the date of randomisation (*i.e*., start of the follow-up period), provided treatment had not been suspended. For these patients, the index date will be assumed to be the date of randomisation.

Each noted suspension of oral anticoagulation and the dates of and reasons for suspension will be recorded during the 12-month follow-up period. The number of days from the index date until treatment is suspended will be calculated. The next noted date of oral anticoagulation use will indicate that treatment was reinstated. Noted use of anticoagulation in the medical record at least once every three months from the index date or date of reinstatement will be assumed to indicate continuous treatment throughout that three-month period in the absence of any recorded suspension of treatment.

Where there are no subsequent dates recording oral anticoagulation use beyond a three-month period, we will assume treatment was suspended three months from the last date recording oral anticoagulation use. Patients without a recorded note of oral anticoagulation will be considered to have had zero days of use.

The number of days of oral anticoagulation use will be summed and divided by the denominator (*i.e*., 365 days) to calculate the percentage of days of anticoagulation use.

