### Follow-up

We define our follow-up period as the 12-month interval following the date practices were randomised (October 13, 2009).

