As practices (clusters) were randomised, we needed to allow for the correlation between the outcomes of patients from the same cluster. We have inflated the sample-size estimate by the design effect (DEFF); DEFF = [1 + (*m *- 1)ρ], where *m *is the average number of patients per cluster and ρ is the intracluster correlation coefficient (ICC) that quantifies the amount of within-cluster correlation for the outcome of interest [37]. An estimate for the ICC for warfarin uptake in patients with atrial fibrillation recruited within general practice clusters is 0.029 [11]. We have conservatively chosen an ICC of 0.04 in recognition of the imprecision with which ρ is estimated. We estimate an average of 20 eligible patients with NVAF per GP will be identified. This estimate assumes an average of 350 eligible patients over the age of 65 per GP, a prevalence rate for NVAF in general practice of ~8.6% [38], that our computerised search strategy will identify 85% of patients with atrial fibrillation, and that 80% of patients will not refuse permission for an independent medical record audit. Based on previous experience of recruiting GPs [39], we expect to recruit an average of 1.25 GPs per practice, yielding an average sample size of 25 patients per practice (1.25 × 20). The estimated DEFF is 1.96 (*i.e*., [1 + (25 - 1)0.04]). Therefore, we require 798 patients per group (*i.e*., 407 × 1.96). Assuming 10% will die, move away during the study, or be lost to follow-up, our revised sample size is 887 per group. We therefore aimed to recruit 36 practices per group (*i.e*., 887 ÷ 25 patients per practice), 72 practices in total, and 90 GPs in total (72 × 1.25 GPs per practice). To further allow for 10% drop out at practice level, we aimed to recruit 40 practices per group (80 in total, or 100 GPs), yielding a total patient sample of 2,000 (100 GPs × 20 patients or 80 practices × 25 patients) or 1,000 per group.

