### Statistical analysis

All outcomes will be analysed according to the intention-to-treat principle, where patients are analysed according to the arm to which their practice cluster was allocated. Analyses of the outcomes will be implemented using marginal logistic regression models using generalised estimating equations (GEEs), with information sandwich ('robust) estimates of standard error to allow for within-cluster (within-general practice) correlation for dichotomous outcomes [40]. An exchangeable correlation structure will be specified for the marginal models using GEEs. Clustering will be accounted for only at the practice level as this is the unit of randomisation. Analyses will adjust for stratification of GPs by LGA.

In addition to unadjusted analyses, we will carry out adjusted analyses to allow for the effect of characteristics, current at the time of randomisation, as noted above.

Percentage of inter- and intrarater agreement and kappa coefficients will be calculated to quantify rates of reliability for the collected audit data [41].

Significance of the study results, specifically, the effect of the intervention on primary and secondary outcomes, will be ascertained by examining the magnitude of the estimated effect of the intervention and corresponding 95% CIs. When testing for interaction terms, a *p *value of < .05 will be used to determine significance of the effect. Analyses will be carried out blinded to group allocation.

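### The percentage-of-time outcome credits anticoagulation for up to three months after a patient dies or leaves, because the derivation has no cut-off at exit, and it then divides by 365 days for everyone

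*Protocol article*

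**What the plan says.** The protocol article, under the secondary outcome on percentage of time anticoagulated, sets four rules.

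- **Continuity.** A note of use at least every three months is taken as "continuous treatment throughout that three-month period in the absence of any recorded suspension of treatment".
- **Carry-forward.** If no later note exists, "we will assume treatment was suspended three months from the last date recording oral anticoagulation use".
- **No notes.** "Patients without a recorded note of oral anticoagulation will be considered to have had zero days of use".
- **Percentage.** "The number of days of oral anticoagulation use will be summed and divided by the denominator", and that denominator is given as "365 days) to calculate the percentage of days of anticoagulation use".

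The Follow-up section fixes the window: "We define our follow-up period as the 12-month interval following the date practices were randomised". The Sample size section expects incomplete follow-up: "Assuming 10% will die, move away during the study, or be lost to follow-up". Losses to follow-up defines a lost patient as one with no GP contact at all in the period, and otherwise only compares the proportions lost or partly followed. The sensitivity analyses for losses cover the primary outcome alone.

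**The concern.** A recorded suspension is the only event the derivation names as ending credit early. Death and departure are not mentioned, and no other section corrects this outcome for them. Applied as written, the rule makes two errors in opposite directions for the same patient. The carry-forward adds days on which the patient was dead or unobserved, and the fixed denominator counts the rest of the year as non-use.

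The result fits neither sensible reading of the outcome. Treated days out of the year cannot include days after death. Share of time at risk cannot have days after death in the denominator. The score therefore partly reflects survival and retention instead of prescribing, and an arm difference in exits would enter the comparison.

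**Working it through.** **Plan's own figures.** The protocol gives no expected value or power for this outcome, so there is none to reproduce. The 10% allowance is a real part of the sample size: 407 × 1.96 = 798, and 798 / 0.90 = 887 per group, as stated.

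**Single patients.** Take three months as 91 days and a patient treated every day until death. Credited days = min(last note + 91, 365).

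| Last note (day) | Death (day) | Credited | After death | Rule, /365 | Stopped at death, /365 | Over days alive |
|---|---|---|---|---|---|---|
| 25 | 30 | 116 | 86 | 31.8% | 8.2% | 100% |
| 80 | 90 | 171 | 81 | 46.8% | 24.7% | 100% |
| 172 | 182 | 263 | 81 | 72.1% | 49.9% | 100% |
| 264 | 274 | 355 | 81 | 97.3% | 75.1% | 100% |
| 330 | 340 | 365 (capped) | 25 | 100% | 93.2% | 100% |

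The maximum is about 91 days after death, or 91/365 = 25 percentage points. The excess needs a recent note: with a last note on day 80 and death on day 182, credit ends on day 171 and no day after death is counted.

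**Share affected.** The 10% pools deaths, moves and losses. Non-users score 0% under any version. If exits are similar in users and non-users, and 50 to 60% are users (rates borrowed from the primary-outcome sample size), the share is 10% × 0.5 to 0.6 = 5 to 6%. Fewer than that receive days after death.

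**Arm means, balanced exits.** Assumptions: each patient is a continuous user or a non-user, exits are uniform over the year, and the last note falls 0–30 or 0–90 days before exit. By simulation, exiting users are credited on average with 69 or 46 days after exit, and score S = 69% or 63%. S is 50% if credit stops at exit (over 365) and 100% over days at risk. With user share p and exit share f, arm mean = p × [(1 − f) × 100 + f × S]. At f = 10%, with p = 50% and 60%:

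- Rule, 0–30 day gap: 48.4 and 58.1, difference 9.7.
- Credit stopped at exit, over 365: 47.5 and 57.0, difference 9.5.
- Over days at risk: 50 and 60, difference 10.0.

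For f from 5% to 20% and either gap, the rule's difference runs from 9.8 down to 9.3. That is about 0.2 to 0.7 points below the days-at-risk figure, and 0.1 to 0.4 points above the stopped-at-exit figure.

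**Unbalanced exits.** Suppose 60% are users in both arms, and exits are 10% in one and 15% in the other. The rule then shows a difference of 0.6 × 0.05 × (100 − 69) = 0.9 to 0.6 × 0.05 × (100 − 63) = 1.1 points with identical prescribing. Days at risk would show 0; treated days out of 365, stopped at exit, would show 0.6 × 0.05 × 50 = 1.5. The rule matches neither.

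**The case against.** Several points in the protocol's defence stand.

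- **The fixed denominator is defensible.** The outcome is defined over a 12-month window, and treated days out of 365 for every patient is a legitimate estimand. Dividing by days alive has its own difficulty: a treated patient who dies on day 30 scores 100%. A reader might infer that the 365 is itself an error. The text does not support that; the error common to both readings is crediting days after exit.
- **Suspension is undefined.** The protocol records dates of and reasons for each suspension, and neither includes nor excludes death. If auditors entered deaths as suspensions, the numerator would stop correctly. That is a hope about practice, not a stated rule.
- **The size is small.** Patients with a life expectancy under 12 months were removed before randomisation, and a marked imbalance in exits would show in the planned comparison of losses. The intervention's own effect on mortality would also be slight. If all 10% of exits were deaths, and a 10-point gain in use carried the 26% mortality reduction cited in the Background, exits would differ by about 10% × 26% × 10% = 0.26 points.
- **The model.** A reader might infer that logistic regression is prescribed for a percentage, since the Statistical analysis section opens with "Analyses of the outcomes will be implemented using marginal logistic regression models using generalised estimating equations". The same sentence goes on to limit this to dichotomous outcomes. The article is silent on the model for this outcome, and an analysis plan may supply it.

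The objection that an article may leave edge cases to a fuller document does not dispose of the point. The carry-forward and the denominator are both stated explicitly, and together they yield the scores above.

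**Conclusion.** The point holds for one secondary outcome and is modest in size. As written, the derivation can credit up to about 91 days of use after death, which no reading of the outcome supports. For patients who move away, the fault differs: up to three months of unobserved use, followed by assumed non-use even though they may still be treated.

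A reader might infer that a tenth of patients are mis-scored or that the arm comparison is seriously biased. Neither follows: about 5 to 6% are affected on the assumptions shown, and the arm difference moves by less than 1 point with balanced exits. An imbalance of 5 percentage points in exits would add roughly another 1 point relative to time at risk. These sizes rest on assumed exit times and note gaps; the individual scores follow directly from the rule. The primary outcome and sample size are untouched.

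**What to change.** 1. Add one sentence to the derivation: credited use ends at the earliest of 12 months from randomisation, death, or recorded departure from the practice. For patients known to have died or left without a date on the audit form, use the last recorded contact.
2. State which measure is intended: treated days out of a fixed 365, or the share of days alive and under observation. Report the other as a sensitivity analysis, and extend the planned sensitivity analyses for losses to this outcome.

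**Cost.** A small amount of derivation code. Dates of death or departure are not among the audit items the article lists, and data collection has begun, so some records may need to be checked again. Percentages over days observed will be noisier for patients with short follow-up; weighting by days observed can address this. Because data are to be cleaned and locked before the group codes are released, the rule can still be set blind to allocation if it is fixed before then.
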